# Maximizing adherence and retention for women living with HIV and their infants in Kenya (MOTIVATE! study): study protocol for a randomized controlled trial

**DOI:** 10.1186/s13063-018-2464-3

**Published:** 2018-01-29

**Keywords:** Text messages, SMS, Community mentor mothers, PMTCT, HIV, Option B+

## Abstract

**Background:**

Successful completion and retention throughout the multi-step cascade of prevention of mother-to-child HIV transmission (PMTCT) remains difficult to achieve. The Mother and Infant Visit Adherence and Treatment Engagement study aims to evaluate the effect of mobile text messaging, community-based mentor mothers (cMMs), or both on increasing antiretroviral therapy (ART) adherence, retention in HIV care, maternal viral load suppression, and mother-to-child HIV transmission for mother-infant pairs receiving lifelong ART.

**Methods/design:**

This study is a cluster randomized, 2 × 2 factorial, controlled trial. The trial will be undertaken in the western Kenyan counties of Migori, Kisumu, and Homa Bay. Study sites will be randomized into one of four groups: six sites will implement both text messaging and cMM, six sites will implement cMM only, six sites will implement text messaging only, and six sites will implement the existing standard of care. The primary analysis will be based on the intention-to-treat principle and will compare maternal ART adherence and maternal retention in care.

**Discussion:**

This study will determine the impact of long-term (up to 12 months postpartum) text messaging and cMMs on retention in and adherence to ART among pregnant and breastfeeding women living with HIV in Kenya. It will address key gaps in our understanding of what interventions may successfully promote long-term retention in the PMTCT cascade of care.

**Trial registration:**

ClinicalTrials.gov, NCT02491177. Registered on 11 March 2015.

**Electronic supplementary material:**

The online version of this article (10.1186/s13063-018-2464-3) contains supplementary material, which is available to authorized users.

## Background

There has been a remarkable increase in the proportion of HIV-infected pregnant women receiving antiretroviral therapy (ART) globally from 37% in 2009 to 77% in 2015 [1]. As a result, an estimated 1.1 million new HIV infections among children have been averted, and AIDS-related deaths among HIV-infected pregnant women have declined by 45% [1]. In 2015, the World Health Organization (WHO) recommended providing lifelong ART to all HIV-infected pregnant and breastfeeding women, regardless of CD4 cell count or clinical stage [2]. This guideline, termed “Option B+,” is expected to lead to even greater declines in both the number of new HIV infections and AIDS-related maternal deaths.

The Option B+ approach was designed in part to reduce barriers to ART initiation for pregnant and breastfeeding women, such as the need for CD4 testing to determine treatment eligibility and complex treatment regimens. However, successful completion and retention throughout the multi-step prevention of mother-to-child HIV transmission (PMTCT) cascade of care remains difficult to achieve, threatening the great potential of this strategy. The Option B+ approach may pave the way to achieving virologic suppression and potentially eliminating mother-to-child HIV transmission, yet the high potential for attrition and disengagement from care increases the risk of morbidity and mortality for both mother and child.

The challenges of achieving success in the PMTCT cascade are perhaps best highlighted in Malawi’s pioneering Option B+ program. In this program, pregnant women who initiated ART for PMTCT had a fivefold higher risk of failure to return to clinic compared to those who started ART for their own health [3]. Retention in PMTCT in this program has varied between 65 and 87% [3–6]. A similar picture of imperfect engagement in care is observed across other sub-Saharan African Option B+ programs: 88% retained at 6 months in Ethiopia [7], 83% retained at 6 months in Zimbabwe [8], 66% retained at 1 year in Ghana [9], and 66% completing postnatal follow-up in Nigeria [10]. Further, among women who initiate ART and are later transferred from PMTCT clinics in the postpartum period to general adult ART clinics, about 25% disengage from care after referral [11]. A systematic review and meta-analysis of 44 studies from 15 sub-Saharan African countries reported significant drop-offs along the cascade of PMTCT care for mother-baby pairs: 70% of HIV-positive pregnant women received antiretroviral prophylaxis, 64% of HIV-exposed infants were tested for HIV using DNA polymerase chain reaction (PCR) at 6 weeks after birth, and 55% were tested between 1 year and 18 months of age [12]. These high rates of attrition reflect the precarious steps along the cascade of care and treatment for pregnant and breastfeeding women living with HIV and their infants. For Option B+ to succeed, it is necessary to identify optimal models of care that support maternal adherence and maternal and infant retention through the care continuum. There is an urgent need to investigate efficacious, cost-effective, and sustainable interventions to improve maternal and infant retention and adherence to lifelong ART in the setting of Option B+.

Existing research documenting evidence-based interventions to promote retention in this population is limited, as reflected by the recently published systematic review of interventions to improve postpartum retention of women in PMTCT and ART care [13]. However, there is growing evidence that community-based interventions that empower people living with HIV and mobile phone interventions may be powerful approaches to improve retention along the PMTCT cascade [14–16]. The Joint United Nations Programme on HIV/AIDS (UNAIDS) highlights the need for community and, in particular, female empowerment [17]. The Government of Kenya supports the principle that women living with HIV must be at the center of the response to the epidemic [18, 19] and also supports a facility-based mentor mother approach as outlined in the Kenya Mentor Mother Program launched in 2012 [20]. Separately, mobile phone interventions have shown promise for supporting service provision and retention of and adherence to HIV programs [21, 22]. In one randomized trial in Kenya, text messaging significantly improved maternal retention in the early postpartum period and increased rates of testing to facilitate early infant diagnosis of HIV [23, 24].

Although mentor mother approaches may enhance adherence and retention in care, little is known about the benefit of supplementing this strategy with mobile phone interventions and implementing the strategy at the community level. Using a 2 × 2 factorial cluster randomized trial, the Mother and Infant Visit Adherence and Treatment Engagement (MOTIVATE!) study aims to evaluate the effect of mobile text messaging, community-based mentor mothers (cMMs), or both on increasing ART adherence, retention in HIV care, maternal viral load suppression, and mother-to-child HIV transmission for mother-infant pairs receiving lifelong ART (Option B+).

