#### cMMs

cMMs are women living with HIV with recent pregnancy experience who support uptake and retention of PMTCT services in their communities. Unlike traditional facility-based mentor mother programs, in this study, cMMs will be based in the community and will conduct home visits for HIV-positive women (together with their male partners if desired) in their respective communities in order to assist with safe disclosure, support safe infant feeding, promote safer sex and family planning, encourage early infant testing and follow-up, and promote ART adherence and return for HIV care visits.

Criteria for selecting cMMs are modeled on Kenya Mentor Mother Program Guidelines [20]. These include being an HIV-positive mother, having recent PMTCT experience (6 months–2 years), attaining a minimum of Standard 8 education, having disclosed HIV status to at least one person within her household, living within the local community, and demonstrating good ART adherence for at least 6 months. cMMs will participate in 2 weeks of initial training that covers basic medical knowledge about HIV infection and ART, behaviors that help prevent mother-to-child transmission, safer feeding options for infants, counseling methods that can help women to safely disclose their status, strategies for negotiating safer sexual practices, and nutritional guidelines for women living with HIV as outlined in the Kenya Mentor Mother National Guidelines [20]. This training will include stigma-reduction and sensitivity training modules.

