
### Study procedures

On-the-job training to strengthen the delivery of fully integrated ANC/MNCH/HIV clinical services will be conducted. Refresher trainings for health care providers at study sites will cover the components of high-quality ANC, PMTCT, and HIV treatment for pregnant women; early infant diagnosis; care and treatment for HIV-exposed infants and HIV-infected children; and postpartum family planning.

Study interventions will begin during pregnancy when the participant is enrolled and continue up to12 months postpartum. Blood sampling and laboratory testing required for primary and secondary study outcomes, including HIV testing for pregnant women and exposed infants, maternal CD4 counts, and viral loads, will be conducted as part of routine care per Kenya National ART guidelines by health facility staff.

We will also establish a Community Advisory Group (CAG) composed of local health workers, community leaders, representatives of community groups, and persons living with HIV in the study communities. This group will be invited to participate in a multi-day workshop to discuss the study plans, refine the content of community outreach messages, and discuss the cMM intervention; as well as in regular meetings throughout the study period. We will work with the CAG to develop methods for introducing the study, obtaining local support, and keeping communities informed about study progress and results.

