### Data collection and measures

Standardized HIV clinic visit forms and clinic registers developed by the Kenyan Ministry of Health (MOH) are used at all patient clinic visits. For this study, a standardized electronic data abstraction form with built-in quality controls has been developed to capture demographic and clinical information from these clinic and patient records. Data will be collected by trained research staff from source documents on a weekly or bi-weekly basis. All participant visits since the last data abstraction will be entered into the electronic form. Research staff will support accurate and thorough documentation by health care providers during routine site visits. Data collection on study participants will continue for a minimum of 12 months postpartum or until study end.

Primary outcome measures include adherence to ART and retention in care at 12 months postpartum. ART adherence will be measured via self-report routinely collected in the woman’s medical record and viral load. Patient adherence is classified by MOH routine data collection tools as good (>95%), fair (85–94%), or poor (<85%) assessed from the last clinic visit, with clear definitions for each of these categories. Viral load measurements will be conducted as per Kenya National ART guidelines after 6 months of ART for those newly initiating (or at time of pregnancy identification for those already on ART). Those with viral load < 1000 copies/mL will be considered virally suppressed. Those with viral load > 1000 copies/mL will be evaluated for evidence of treatment failure or poor adherence. Our primary outcome for retention in care will be obtained from the women’s clinic visit history and is defined as the proportion of women who have an HIV care visit within 90 days at 12 months after delivery. Data will be shared in agreement with funder (National Institutes of Health, NIH) data sharing policies. Results will be disseminated to local stakeholders (including participants) through local presentations, regional/national/international conferences, and publications.

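### Infant infection is observed only through routine testing, which both interventions are designed to increase, so comparing positive tests by arm can be biased against an effective intervention

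*Protocol article*

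**What the plan says.** The Abstract and the Background both list mother-to-child transmission among the effects to be evaluated; the Background has "maternal viral load suppression, and mother-to-child HIV transmission for mother-infant pairs receiving lifelong ART (Option B"+).

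Under Study procedures, the testing needed for primary and secondary outcomes, "including HIV testing for pregnant women and exposed infants, maternal CD4 counts, and viral loads, will be conducted as part of routine care", is done by health facility staff. Under Data collection and measures, an electronic form is used "to capture demographic and clinical information from these clinic and patient records". The article describes no infant test run by the study.

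Both interventions act on attendance for testing. The cMMs section has the mentor mothers "encourage early infant testing and follow-up, and promote ART adherence and return for HIV care visits", and their visits are timed to match infant testing schedules. Text message content follows the PMTCT and child health schedule, and the Background supports it with a Kenyan trial in which messaging raised early infant testing. Primary analyses lists time to infant testing as a secondary outcome.

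On completeness, the review cited in the Background found 64% of exposed infants tested at 6 weeks, while "55% were tested between 1 year and 18 months of age". On duration, "Data collection on study participants will continue for a minimum of 12 months postpartum or until study end".

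Secondary analyses plans for perhaps 20% of individuals who cannot be located: multiple imputation under MAR from baseline covariates, a sensitivity analysis for departures from MAR, and possibly inverse probability of censoring weighting (IPCW).

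**The concern.** An infection counts only if the infant was brought for a test. If an intervention raises testing, it also raises the share of infections that are seen. Two distortions can follow.

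- Over all infants, more testing finds more cases even when true risk is equal.
- Among tested infants, the intervention group includes infants who would have gone untested under standard care. If those infants come from less engaged pairs with higher risk, positivity rises with no change in transmission.

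Both distortions work against the intervention. At stake is the conclusion on a stated aim: a protective intervention could be reported as having little effect, or as harmful.

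**Working it through.** **Figures in the plan.** No rate difference, power or event count is given for transmission, so there is no stated result to reproduce. The total of 1336 does reproduce. For retention (48% v 73%), the continuity-corrected size is 67 per group. With ICC 0.12, mean cluster size 70 and a coefficient of variation of (130 − 50)/4/70 = 0.286 (my assumption from the stated range), the design effect is 1 + [(1 + 0.286²) × 70 − 1] × 0.12 = 9.97, and 2 × 67 × 9.97 ≈ 1335. Half of 1336 is 668 mother-infant pairs per level of each factor.

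**Inputs from the article.** Transmission 10% (Study setting and sites); infant testing 64% or 55% (Background); planned retention 48% v 73% (Power and sample size estimation).

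**Assumptions.** Intervention testing of 80%. A risk *k* times higher in infants who would be untested under control conditions than in those who would be tested. A true risk ratio θ that applies to all infants equally. The 64% and 55% come from a multi-country review, so using them for these sites is also an assumption.

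**Formulas.** Let t₀ and t₁ be the shares tested.

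- Control risk among tested: r = 0.10 / [t₀ + (1 − t₀)k]
- Intervention risk among tested: θ·r·[t₀ + k(t₁ − t₀)] / t₁
- Observed risk ratio among tested: θ·[t₀ + k(t₁ − t₀)] / t₁
- Observed risk ratio for detected infections over all infants: θ·[t₀ + k(t₁ − t₀)] / t₀

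**Worked case, 55% v 80%, k = 3, θ = 1.** r = 0.10/(0.55 + 1.35) = 5.3%. Intervention: 5.26% × (0.55 + 0.75)/0.80 = 8.6%. Odds ratio 1.68. Over all infants, 0.55 × 5.26% = 2.9% v 0.80 × 8.55% = 6.8%.

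**Range.**

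| Tested | k | No effect: OR among tested | True RR 0.60: shown among tested | True RR 0.60: shown over all |
|---|---|---|---|---|
| 55% v 80% | 1 | 1.00 | 0.60 | 0.87 |
| 55% v 80% | 2 | 1.34 | 0.79 | 1.15 |
| 55% v 80% | 3 | 1.68 | 0.975 | 1.42 |
| 55% v 80% | 4 | 2.02 | 1.16 | 1.69 |
| 64% v 80% | 1 | 1.00 | 0.60 | 0.75 |
| 64% v 80% | 2 | 1.22 | 0.72 | 0.90 |
| 64% v 80% | 3 | 1.44 | 0.84 | 1.05 |
| 64% v 80% | 4 | 1.65 | 0.96 | 1.20 |

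**No excess risk in the untested (k = 1), all infants as denominator.** If testing tracked planned retention, a true 10% v 8% would show 10% × 0.48 = 4.8% v 8% × 0.73 = 5.8%, about 32 v 39 cases in 668. The break-even intervention risk is 10% × 0.48/0.73 = 6.6%. With 64% v 80% tested it is 10% × 0.64/0.80 = 8.0%.

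**Would a composite avoid this?** In the worked case with no effect, tested and HIV-negative is 0.55 − 0.029 = 52.1% v 0.80 − 0.068 = 73.2%, an apparent gain of 21 points that comes from testing alone.

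**The case against.** The article states neither a denominator for transmission nor a plain comparison of positive tests. Its open list of secondary outcomes does not name transmission, and an article may leave the definition to the full protocol or SAP. That stands, so a missing definition is not the finding. The finding is that the way infection is ascertained is itself affected by the interventions, whichever denominator is used.

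The plan does address missing outcomes. Non-MAR sensitivity analysis is the right kind of tool, and the weighting model allows previous history as well as baseline. This lessens the problem but does not remove it. The section concerns women who cannot be located, perhaps 20%, whereas the cited review implies 36% to 45% of infants untested. Some of those may have mothers still in care. The imputation model named uses baseline covariates only, and the weighting is only to be considered.

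The testing difference is itself uncertain. The Discussion cites a Kenyan cluster trial of text messages that did not increase infant testing. With equal testing and the same kind of infants tested in each arm, this bias disappears.

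A reader might infer that the 12-month end of assured data adds to a reversal. The documents do not support this: the limit is the same in every arm and is a stated minimum. It restricts what the result covers, not its direction.

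**Conclusion.** The concern holds as a possibility that the design leaves open, not as a prediction. Over all infants, a higher testing rate alone is enough to bias the comparison. Among tested infants, the bias also needs higher risk in those otherwise untested; at equal risk there is none.

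A reader might infer that the trial will show a protective intervention as harmful. The figures do not support so strong a statement. With 64% v 80% tested, a true 40% reduction stays visible among tested infants (0.72 to 0.84 at two- to threefold risk). With 55% v 80% and threefold risk it all but vanishes (0.975), and over all infants it reverses (1.42). Intervention testing and excess risk are assumed throughout, and the 55% belongs to a testing window that begins where assured follow-up ends.

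Transmission is not a primary outcome and carries no power claim, so the comparisons of adherence and retention are untouched. This is a cheap improvement to how a secondary aim is reported.

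**What to change.** 1. Report any transmission result only beside the proportion of infants tested, by arm.
2. Extend the missing-data plan explicitly to untested infants, including those whose mothers remain in care, and use post-baseline engagement such as visit history as well as baseline covariates.
3. Add bounds or a non-ignorable sensitivity analysis for untested infants. Extreme bounds are as wide as the untested share (36 points at 64% tested, 20 points at 80%), so also vary the relative risk in the untested over a stated range and report where the conclusion changes.
4. State that the result refers to infection detected by 12 months.
5. Optionally add the proportion of all live-born infants known to be HIV-negative at 12 months as a supportive service outcome. Label it as mixing testing uptake with infection status. It must not stand in for the transmission effect, because it is biased in the intervention's favour when testing rises.

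Cost: a little extra analysis, mostly of records already being abstracted, and wider, less definite conclusions on a secondary aim. The article does not say whether live birth and infant survival are abstracted, so the optional outcome needs that checked. With the trial at month 44 of 60, this can still be fixed before analysis.

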## Methods/design

### Study setting and sites

The focus of this work is in Migori, Kisumu, and Homa Bay counties in Kenya. With 14.3% (Migori), 19.9% (Kisumu), and 26% (Homa Bay) of adults 15–49 years of age testing HIV-positive in 2015, this region has the highest HIV prevalence in Kenya [25]. Kenya officially adopted Option B+ for pregnant and breastfeeding women in 2014, with rollout thereafter. This setting has several characteristics that make it a priority area for research on the implementation of Option B+ among HIV-positive pregnant women and their families, including (1) high HIV prevalence among pregnant women (20%), (2) high rates of MTCT of HIV (10%), and (3) low retention for women who test HIV-positive at antenatal care (ANC) clinics [26, 27]. This study will be conducted at 24 low-resource primary health care facilities in the selected counties. All study facilities provide PMTCT services including Option B+ integrated into the ANC clinic.

### Study design

This study is a cluster randomized, factorial, controlled trial. Using a 2 × 2 factorial design, we will evaluate the effect of cMMs, text messaging, or both on service utilization and maternal and child health outcome indicators. Study sites will be randomized into one of four groups: six sites will implement both interventions, six sites will implement the cMM intervention only, six sites will implement the mobile phone text message intervention only, and six sites will implement the existing standard of care only (Fig. 1). Randomization will be stratified by geographic region such that each unique geographic region will have at least one site in each study arm. The study employs a unique participatory community randomization approach. Site representatives and key stakeholders will be invited to a centralized randomization meeting in which a representative from each site chooses a sealed opaque envelope from a jar; the envelope reveals their site’s randomization arm.

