### Primary analyses

Preliminary analyses will summarize characteristics of the intervention and control women and assess frequency distributions of variables to identify outlying or unusual values. Initial analyses of our primary outcomes of maternal ART adherence and maternal retention in care (dichotomous variables) will be based on comparisons of proportions between intervention and control groups using cluster-adjusted chi square tests. Although there are only 24 clusters, each mean or percentage will be based on a relatively large number of women, and the normal approximation to the binomial distribution can be used. These tests will be evaluated based on a two-sided alternative hypothesis with a 5% type I error rate. Given the clustered study design, generalized estimating equation (GEE) models will be used to test for differences of interest in univariate and multi-variable models, adjusted for relevant covariates (such as time on ART), using logistic links for these binary outcomes. Secondary outcomes, such as time to infant testing uptake, maternal viral load suppression, and changes in maternal CD4 counts, will be analyzed using similar methods, taking into account the nature of the dependent variable (continuous, dichotomous, or time to event). Results will be summarized as odds ratios for models based on binary responses (e.g., enrollment in HIV care), hazard ratios for time-to-event outcomes (e.g., time to infant HIV test), and mean changes for continuous responses (e.g., maternal CD4 count); respective 95% confidence intervals will also be reported based on the robust variance estimates from the GEE models.

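### Region stratifies the randomisation of sites but is not named in the primary analyses; if region is related to outcome, an otherwise valid unstratified test is conservative and loses precision.

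*Protocol article*

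**What the plan says.** Under Study design, the protocol article allocates the sites, six per arm in a 2 × 2 factorial: "Randomization will be stratified by geographic region such that each unique geographic region will have at least one site in each study arm". The number of regions is not given. Study setting and sites names three counties ("The focus of this work is in Migori, Kisumu, and Homa Bay counties in Kenya") and 24 facilities.

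Under Primary analyses, the initial analysis of both primary outcomes consists of "comparisons of proportions between intervention and control groups using cluster-adjusted chi square tests", evaluated against a "two-sided alternative hypothesis with a 5% type I error rate". In addition, "generalized estimating equation (GEE) models will be used to test for differences of interest in univariate and multi-variable models", the latter "adjusted for relevant covariates (such as time on ART), using logistic links for these binary outcomes". For the intervals, "respective 95% confidence intervals will also be reported based on the robust variance estimates from the GEE models".

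Region appears neither in Primary analyses nor in Secondary analyses, and the sample size section and Table 1 contain no stratification term. The article does not say which of the named analyses is decisive. The full analysis plan is not shown.

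**The concern.** When arms are balanced within region, differences between regions cancel out of the treatment contrast. An analysis that ignores region still counts those differences in its error term, so its standard error is larger than the design warrants. An otherwise valid test then rejects less often than its nominal 5% under the null and gives up precision that the stratified allocation made available.

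The chi-square comparison as described has no region term, and a univariate GEE cannot hold one. This is therefore more than a detail left for later: unstratified tests are named for a stratified design. What is at stake is precision, above all if the true effects are smaller than the 25 points planned for. The article itself allows for this when its Discussion says that concurrent programmes at the sites may attenuate the effect.

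**Working it through.** **Inputs from the protocol article.** 24 sites, so 12 v 12 for each main effect; N = 1336; ICC 0.06 to 0.12; retention 48% v 73%; adherence 55% v 80%; average cluster size 70, range 50 to 130; two-sided alpha 0.05; 80% power.

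**Assumptions.** The share f of between-site variance due to region is not in the documents; 0, 10%, 25% and 50% are used. Each region needs a site in each of four arms, so there can be at most 24/4 = 6 regions; 3 and 6 are used. Arms are taken as exactly balanced within region.

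**Step 1: the plan's own sample size.** With a continuity-corrected two-proportion formula, retention needs 67 women per group and adherence 62. Taking the cluster-size SD as range/4 (an inference), cv = 20/70 = 0.286. The design effect at ICC 0.12 is 1 + [70 × (1 + 0.286²) − 1] × 0.12 = 9.966.
- Retention: 67 × 9.966 rounds up to 668, and 2 × 668 = 1336.
- Adherence: 62 × 9.966 rounds up to 618, and 2 × 618 = 1236.

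Both match Table 1 exactly, and all 14 rows agree within 2 women. The formula is a two-group comparison with no gain assumed from stratification.

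**Step 2: standard error of a main effect on retention.** Mean p = (0.48 + 0.73)/2 = 0.605, so p(1 − p) = 0.2390. Women per site m = 1336/24 = 55.7. At ICC 0.12 the between-site variance is 0.12 × 0.2390 = 0.02868 and the within-site part is 0.88 × 0.2390/55.7 = 0.00378.

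- Region ignored: SE = √[(0.02868 + 0.00378) × 2/12] = 0.0735.
- Region fitted: SE = √[((1 − f) × 0.02868 + 0.00378) × 2/12].
- Type I error with region ignored = 2 × [1 − Φ(1.96 × ratio of the two SEs)].

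| f | SE, region ignored | SE, region fitted | Ratio | Type I error, region ignored |
|---|---|---|---|---|
| 0 | 0.0735 | 0.0735 | 1.00 | 5.0% |
| 10% | 0.0735 | 0.0702 | 1.05 | 4.0% |
| 25% | 0.0735 | 0.0649 | 1.13 | 2.6% |
| 50% | 0.0735 | 0.0549 | 1.34 | 0.9% |

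At ICC 0.06 the ratios are 1.000, 1.041, 1.115 and 1.281.

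**Step 3: power of a cluster-level analysis.** 20,000 simulated trials per cell, ICC 0.12, three regions except where marked, region ignored v fitted:

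| f | 25-point effect | 15-point effect |
|---|---|---|
| 0 | 90.3% v 90.0% | 48.1% v 46.7% (six regions) |
| 10% | 90.7% v 92.1% | 47.4% v 50.4% (six regions) |
| 25% | 91.8% v 95.6% | 45.9% v 57.2% |
| 50% | 94.3% v 99.1% | 44.6% v 72.5% |

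For the planned effect, ignoring region costs 1.4, 3.8 and 4.8 points at f = 10%, 25% and 50%. For a 15-point effect it costs 11.3 and 27.9 points at 25% and 50% (10.2 and 26.8 with six regions).

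Analytic check at f = 25% and 15 points. With region ignored (t on 21 df = 2.080), power = 1 − Φ[(2.080 × 0.0735 − 0.15)/0.0649] = 48.2%. With region fitted (noncentral t, 19 df), it is 59.2%. The gap is 11.0 points.

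**Step 4: the GEE as written.** Type I error in individual-level logistic GEE simulations at ICC 0.12. The robust columns use 400 runs and a z test. The corrected columns use 500 runs, a bias-reduced variance, a t reference and three regions. Monte Carlo error is about 1 to 1.5 points for the robust columns.

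| f | Robust, no region (3 / 6 regions) | Robust, region fitted (3 / 6) | Corrected, no region | Corrected, region fitted |
|---|---|---|---|---|
| 0 | 9.0% / 5.5% | 10.7% / 11.0% | 3.8% | 3.4% |
| 25% | 5.0% / 5.2% | 11.5% / 12.8% | 1.2% | 2.6% |
| 50% | 2.0% / 2.0% | 10.5% / 13.3% | 0.2% | 2.4% |

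A separate simulation of the uncorrected GEE with five region terms gave about 14%. Power of the corrected GEE for the 25-point effect, region ignored v fitted, was 85.8% v 83.2% (f = 0), 86.8% v 89.2% (25%) and 88.6% v 97.6% (50%).

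**The case against.** The strongest reply is that the article condenses a fuller plan and that its covariate list is introduced by an example, so region may well be in the multivariable GEE. That stands: the omission is established only for the chi-square and the univariate GEE, and the chi-square is described as an initial analysis.

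Two stronger conclusions that a reader might draw also fail.

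- **That the planned intervals will be too wide.** This needs a region effect, on which the documents give no figure. The county HIV prevalences (14.3%, 19.9%, 26%) describe adults in general, not adherence or retention among enrolled women. The stated robust variance, for which the article names no small-sample correction, also pushes the other way with 24 clusters. In Step 4 the robust GEE without region ran at 5.0% to 9.0% for f up to 25% and fell to 2.0% only at f = 50%.
- **That the trial is underpowered or has wasted power it counted on.** Table 1 assumed no gain from stratification, 24 sites are used where 20 were required, and power for the planned effect exceeds 80% in every case examined.

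What remains is that the opposing errors are of unknown size and cannot be relied on to cancel. Once the variance is corrected, as it should be with 24 clusters, ignoring region makes the test markedly conservative: 1.2% at f = 25% and 0.2% at f = 50%.

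**Conclusion.** The point holds in conditional form. The randomisation is stratified by region, the chi-square and univariate GEE are not, and the multivariable GEE is silent on region. If region is related to adherence or retention, an otherwise valid unstratified test has a standard error too large by about 5% to 34% at ICC 0.12, for an assumed region share of 10% to 50%; at a share of zero nothing is lost. The consequence is small for the planned 25-point effect and material only for smaller effects, such as 15 points with a share of 25% or more. Omitting region creates no bias and no excess of false positives.

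The sizes rest on the assumed region share, 3 or 6 regions, exact balance within region and, for power, the top of the plan's ICC range. This is a free or cheap improvement, not a flaw that threatens the trial.

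**What to change.** Name the randomisation region as a prespecified fixed effect in the primary GEE for both primary outcomes, or replace the unstratified chi-square with a region-stratified cluster-level test. State the number of regions and which analysis is decisive.

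Pair the region terms with a small-sample variance correction and a t reference. Added to the uncorrected robust GEE, they would make the false-positive rate worse.

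The cost is 2 to 5 degrees of freedom for 3 to 6 regions, and no new data. If region turns out to explain nothing, the price in a cluster-level analysis is about 0.3 points of power with three regions (90.3% v 90.0%) and 0.9 points with six (90.1% v 89.2%). In the corrected GEE with three regions it was about 3 points (85.8% v 83.2%, from 500 runs), which is still above the planned 80%.
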